### Assessment Methods

2.7

#### Assessment of Parameters in Blood

2.7.1

At baseline and at 8 weeks completion, overnight fasted venous blood samples (approximately 29 mLs) will be taken by qualified blood collection staff at Monash Health Pathology into four tubes containing appropriate preservatives for different tests. All the serum and plasma samples will be stored at −80 degrees Celsius until batch analysis at the completion of the study. Vitamin C, oxalate and isoprostane levels will be analysed at Deakin University while all others at Monash Health Pathology.

The collected samples will be analysed by Monash Health Pathology for the measurement of glycaemic control, lipids, liver and kidney functions and micronutrients. HbA1c for glycaemic control will be measured by capillary electrophoresis in fresh ethylenediaminetetraacetic acid (EDTA) whole blood in real time at Monash Health Pathology. Glycaemic control will also be assessed by fasting serum glucose from the glucose oxidase assay and insulin by immunoassay. Blood lipid profile will be assessed by fasting serum cholesterol (total cholesterol and HDL‐cholesterol by direct measurement, and LDL‐cholesterol by calculation using the widely used Friedewald equation [31]) and triglycerides. Liver (serum gamma glutamyl transpeptidase, alkaline phosphatase, alanine aminotransferase, albumin and bilirubin) and kidney (serum urea and eGFR) function tests, lipids, vitamin B12 and vitamin D are measured in serum, while zinc in plasma from lithium heparin trace metal tubes using the Beckman Coulter automatic chemistry or immunoassay analysers.

Aliquots of EDTA with dithiothreitol added (EDTA + DTT) plasma [32] will be frozen and stored at Deakin University at −80 degrees Celsius until the conclusion of the study where it will be analysed for vitamin C [33, 34, 35], oxalate [36] and isoprostane levels [33]. Vitamin C will be measured by high performance liquid chromatography with UV detection [33, 34, 35], oxalate with liquid chromatography–tandem mass spectrometry [36] and isoprostanes (for the measurement of oxidative stress) levels by gas chromatography‐mass spectrometry [33].

#### Collection of Health Information From Each Participant

2.7.2

At baseline, information will be collected in person by the research team regarding demographics, smoking status, alcohol intake, prior foot ulceration and medical history.

The following data will also be collected at baseline and then immediately after the 8‐week treatment (Figure 1): Height, weight, waist and hip circumference; evidence of any endovascular procedures, absence or presence of peripheral neuropathy (assessed via 10g Semmes‐Weinstein monofilament test) [37], current medication and supplement use, brachial blood pressure and peripheral arterial perfusion. The participant will be examined for scurvy signs and symptoms. Measures of mental health and well‐being and dietary intake will be obtained in person by members of the research team using validated short surveys.

#### Ulcer Assessment

2.7.3

Ulcer assessments and measurements will be collected in person by two qualified and experienced (6 and 15 years) Podiatrists at Monash Health who are members of the research team. The number of current ulcers will be recorded. If the participant has more than one ulcer, the largest ulcer will be chosen as the index ulcer [38]. Thereafter, data will only be collected on the index ulcer for this study. Ulcers will then be classified via the Site, Ischaemia, Neuropathy, Bacterial Infection, and Depth (SINBAD) score [39], the WIfI (Wound, Ischaemia, foot Infection) classification [39] and aetiology (neuropathic, ischaemic or neuroischaemic). Ulcer duration and whether the wound is probing to bone, tissue microbiological culture results and any treatment as part of standard care, such as treatment for infection, revascularisation or pressure offloading will be recorded [38]. Amputation outcomes will also be collected, and participants undergoing amputations will be considered not to have healed ulcers.

Ulcer size will be determined by measuring the ulcer length and width with a paper ruler and the depth with a metal probe to calculate the volume in mm^3^. This approach is widely used in a clinical setting [40, 41, 42]. Bedside excisional debridement of nonviable tissue will be conducted prior to wound measurements [28]. Ulcer length will be recorded as the maximum diameter of the ulcer, while ulcer width will be taken as the perpendicular diameter to ulcer length. The ulcer area will be calculated using the ellipse formula [41] and ulcer volume calculated as ulcer area × ulcer depth. A digital image of the wound will also be captured. Interobserver reliability of standard ruler measurements has previously been reported to be excellent for both estimated area (Intraclass correlation coefficients (ICC) 0.98, 95% CI 0.97–0.98) and depth using a probe (ICC 0.93, 95% CI 0.90–0.95) [41]. Also, at the beginning of the study, both Podiatrists underwent the same training according to standard operating procedures for wound measurement that we developed for the trial based on the IWGDF Practical Guidelines (2023 update) [28] and the reliability of wound measurement study by Lasschuit et al. [41].

#### Brachial Blood Pressure

2.7.4

Brachial blood pressure will be assessed in a supine rested position using an automated sphygmomanometer with the average of three measurements taken 3 min apart. Both arms will be measured and the value from the highest arm will be taken as brachial blood pressure [43].

#### Peripheral Arterial Perfusion

2.7.5

Small vessel arterial perfusion and presence of peripheral artery disease will be assessed by measuring systolic toe pressures using the photoplethysmography technique [44] and calculating the toe‐brachial pressure index [45].

#### Scurvy Signs and Symptoms

2.7.6

Symptoms and signs of latent and manifest scurvy will be assessed by a clinical assessment involving an in‐person interview asking participants if they are experiencing scurvy symptoms followed by an examination of the participants' scalp, mouth and skin of their trunk, arms and legs, for signs of scurvy [46, 47].

#### Mental Health and Well‐Being

2.7.7

Given the high prevalence and impact on health [48], mental health outcomes will be recorded using the Diabetes Distress Screening Scale (DDS17), Centre for Epidemiologic Studies Depression (CES‐D) Tool and the Quality of Life Enjoyment and Satisfaction Questionnaire Short Form (Q‐LES‐Q‐SF) as described [49, 50, 51].

#### Dietary Intake

2.7.8

A 24‐h diet recall will be used to assess the macronutrient and vitamin C intake using the Easy Diet Diary platform created by Xyris Software and linked to the FoodWorks database [33, 52] containing the nutrient content of > 40,000 different foods available in Australia.

### Outcome Measures

2.8

#### Primary Outcome

2.8.1

The primary outcome measure is the percentage reduction in ulcer size (ulcer volume in mm^3^) at 8 weeks, compared to baseline. We based our treatment length on the intervention published by Gunton et al. who found in an RCT of 16 participants that percentage ulcer healing at 8 weeks (percentage reduction in ulcer size) was significantly better in people following vitamin C treatment at median 100% compared with −14% following placebo [22]. The minimal clinically important difference is considered a 50% improvement in ulcer size after 4 weeks of treatment and is a robust predictor of complete healing in DFUs [53] and is also considered a large effect size [22, 54]. The ulcer will be considered 100% healed when the epithelium is completely intact. Outcome measures and time points are shown in Figure 1.

#### Secondary Outcomes

2.8.2

##### Wound Healing

2.8.2.1

The following secondary outcomes measures for wound healing are based on the measurement of ulcer volume and will be assessed by measuring at baseline and then every 2 weeks during the 8‐week treatment: (i) Time to 50% ulcer healing; (ii) Time to complete ulcer healing; (iii) Percentage of participants with 50% ulcer healing at 8 weeks and (iv) Percentage with complete ulcer healing at 8 weeks; with the ulcer being considered 100% healed when the epithelium is completely intact.

##### Vitamin C Status

2.8.2.2

Vitamin C status will be assessed by measuring fasting plasma vitamin C at baseline and immediately after the 8‐week treatment. Although vitamin C depletion/hypovitaminosis is not universally defined, we have defined the following criteria for plasma vitamin C status (μmol/L): Normal ≥ 23; Depletion 22.9–11.4; Deficient < 11.4 [19, 46].

#### Exploratory Outcomes

2.8.3

All exploratory outcomes will be measured at baseline and then immediately after the 8‐week treatment for glycaemic control, brachial blood pressure, peripheral arterial perfusion, scurvy signs and symptoms, blood lipid profile, oxidative stress and mental health and well‐being.

### Adverse Events

2.9

Adverse events will be assessed and documented at every fortnightly visit for each participant by asking them whether they have experienced any unusual symptoms or medical problems since their previous study visit. As much detail as possible regarding the nature, severity and duration of the adverse event will be recorded. Bloating and diarrhoea are uncommon side effects of vitamin C supplementation and thus considered adverse reactions rather than adverse events, but they will still be documented and reported in any publication. Serious adverse events will be defined as events that result in death, are life‐threatening, require hospitalisation or the prolongation of an existing hospitalisation, or lead to persistent or significant disability or incapacity [55]. Participants will also be provided with 24‐h contact information for the study team and are encouraged to report any issues that may require medical attention.

### Concomitant Care and Interventions

2.10

At every fortnightly visit following baseline, study staff will inquire about and record any changes to participants' medication/s, supplement usage or ulcer treatment. Participants will also be asked if they have seen a doctor or been hospitalised for any other medical reasons since their last visit.

### Intervention Adherence

2.11

At every fortnightly visit following baseline, study staff will inquire about and record participants' adherence with the study treatment. Remaining capsules will be counted by returned bottles at the end of the 8‐week treatment period. Capsule compliance will be calculated as: (number capsules consumed divided by total number of capsules for 100% compliance) × 100%.

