### Intervention

2.2

Adults with a DFU will be recruited and undergo placebo or vitamin C supplementation in a double‐blind, randomised manner. The treatments will consist of oral ingestion of either vitamin C (500 mg ascorbic acid per capsule, two capsules per day; so, a total of 1 g/day) or placebo (microcrystalline cellulose capsule, two capsules per day) for 8 weeks. A placebo group as the comparator is considered the most rigorous test of treatment efficacy for evaluating a medical therapy in a double‐blind RCT [27]. Participants will be instructed to take one capsule in the morning and one capsule in the evening alongside meals. All outcome measures will be conducted at the beginning (baseline) and then at 8 weeks of treatment. Outcome measures for wound healing will also be recorded at fortnightly visits to the clinic during the 8‐week treatment period (Figure 1). The trial will conclude for each participant at 8 weeks or beforehand if the patient undergoes amputation or withdraws consent.

All participants will continue to receive usual standard of care throughout the trial. Standard care was defined according to the IWGDF Practical Guidelines (2023 update) [28] and comprised core evidence‐based prevention and management practices for DFD. This included routine risk‐based foot screening using structured assessments for neuropathy, peripheral artery disease, deformity, callus, pre‐ulcerative lesions, and any history of ulceration or amputation. Participants also received education on daily foot inspection, protective footwear use, foot hygiene, and prompt escalation for any foot concerns. Standard care additionally involved appropriate offloading and therapeutic footwear to reduce plantar pressure, as well as timely ulcer classification and management using best practice wound care and coordinated evaluation of infection or peripheral artery disease within a multidisciplinary model.

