### Statistical Analysis

2.15

Primary analyses will be conducted on an intention‐to‐treat basis. Treatment effects for continuous outcomes will be estimated using linear regression models, adjusted for stratification variables study site and baseline ulcer size, and where relevant also baseline level of the outcome. For time‐to‐event outcomes, time to 50% healing and time to complete healing, we will conduct survival analysis, including Kaplan–Meier curves and Cox proportional hazards models (adjusted for study site and baseline ulcer size). Multiple imputation by chained equations will be used to handle missing outcomes data (except for censored time‐to‐event data). Per‐protocol analysis will also be performed on all participants who are > 90% capsule compliant. Complete case analysis will also be conducted to examine if results were sensitive to the approach for handling missing data. Statistical analyses will be conducted using Stata/SE 17.

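### The per-protocol set is defined by capsule count alone, so placebo participants who take vitamin C outside the trial stay in it

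*Protocol article*

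**What the plan says.** All references are to the protocol article.

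- **Per-protocol set (2.15).** After making intention-to-treat primary, the section adds that a per-protocol "analysis will also be performed on all participants who are > 90% capsule compliant". No second condition is given.
- **Compliance (2.11).** The percentage is "number capsules consumed divided by total number of capsules for 100% compliance", times 100. On timing: "Remaining capsules will be counted by returned bottles at the end of the" 8-week period.
- **Regimen (2.2).** The article gives "two capsules per day) for 8 weeks".
- **Outside vitamin C.** Section 2.4 excludes people who already take a vitamin C supplement. Section 2.10 has staff ask at each fortnightly visit after baseline about changes in medication, "supplement usage or ulcer treatment". Neither section says what later vitamin C use means for the per-protocol set.
- **Early end.** Section 2.2 says: "The trial will conclude for each participant at 8 weeks or beforehand if the patient undergoes amputation or withdraws consent". Section 2.7.3 adds that "participants undergoing amputations will be considered not to have healed ulcers".
- **Withdrawals (2.12).** Data from withdrawn participants, including those with an amputation or a protocol violation, go into the intention-to-treat analysis. Adherence figures are not substituted.

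**The concern.** A per-protocol analysis should estimate the effect of vitamin C against no supplementation among people who followed the plan. Following the plan has two parts here: taking the assigned capsules, and not obtaining the active ingredient elsewhere. The entry criterion shows that the trial regards outside vitamin C as incompatible with the comparison, yet the set tests only the first part.

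A supplemented placebo participant can thus count as fully adherent. Such participants move the placebo result towards the vitamin C result, so the analysis meant to show the cleanest contrast shows a diluted one. Outside use is plausible: the Discussion calls the trial dose common and commercially available, and participants know what is being tested.

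The capsule count also decides, without saying so, what happens to participants who stop early for amputation. That bears on how the result is read and is treated below as a clarification.

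**Working it through.** **1. The plan's own figure.** Section 2.14 uses d = 0.80, two-sided α = 0.05 and 90% power. A two-sample t-test needs 33.83, so 34 per group (power at 34 is 0.902) and 68 in total. Allowing for 15% withdrawal, 68 / 0.85 = 80. The stated 68 and 80 reproduce, and nothing below changes them.

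**2. Does the rule detect outside vitamin C?** Two capsules a day for 8 weeks is 2 × 56 = 112 capsules. This total is derived; the article does not print it. A placebo participant who takes all of them scores 112/112 = 100%. Outside vitamin C enters neither numerator nor denominator, so the score stays at 100%. The same holds if the denominator is the number of capsules due up to an earlier stop. This result does not depend on how 2.11 is read.

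**3. Size of the dilution.** Let Δ be the true difference, f the share of placebo participants in the set who take outside vitamin C, and k the fraction of the full effect they obtain. The placebo mean moves by k·f·Δ, so the observed contrast is Δ(1 − k·f). With k = 1, the upper limit, f = 10% leaves 0.90Δ. With k = 0.5 it leaves 0.95Δ.

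With k = 1, the planned d and 34 per group for illustration:

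| f (assumed) | d = 0.80 × (1 − f) | Power |
|---|---|---|
| 0% | 0.80 | 90% |
| 5% | 0.76 | 87% |
| 10% | 0.72 | 83% |
| 20% | 0.64 | 74% |

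The documents give neither f nor k. The actual per-protocol set may also differ in size from 34 per group, so the power column shows the trend only.

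**4. Clarification on early stopping.** On the 112-capsule denominator, more than 90% means more than 0.90 × 112 = 100.8, so at least 101 capsules. A participant who misses none and stops on day t scores 2t/112:

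- week 4: 56/112 = 50%
- week 6: 84/112 = 75%
- day 50: 100/112 = 89.3%, dropped
- day 51: 102/112 = 91.1%, kept

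On this reading a perfect adherer whose treatment ends by day 50 is outside the set.

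**The case against.** **The article is condensed.** Further per-protocol criteria may sit in a full protocol or analysis plan that is not shown, and silence in an article is no fault. That is fair in general. But 2.15 is not silent: it admits all participants who pass a single test, which is a complete rule. Section 2.12 names protocol violation as a reason for withdrawal, which could catch outside vitamin C, but no text defines such use as a violation.

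**The exclusion is itself a selection after randomisation.** It would also remove vitamin C participants who take extra vitamin C, although the dilution arises in the placebo group. This stands as a cost. It is the ordinary price of a per-protocol set, and applying the same rule to both groups lets the set be fixed before unblinding.

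**Little depends on it.** The analysis is supplementary, and outside use would dilute the intention-to-treat contrast as well. This stands and limits the severity.

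**A stronger reading.** A reader might infer that the rule biases the estimate by removing adherent treatment failures, namely amputees. The documents do not carry that far:

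- The 112-capsule denominator is the natural reading, given a count at the end of 8 weeks, but it is not printed. Capsules due up to the stop is possible, and then nobody is dropped for this reason.
- Leaving non-completers out of a per-protocol set is conventional. The aim concerns an 8-week course, and 2.12 keeps amputees in the intention-to-treat analysis.
- Any size depends on assumptions. Suppose mean reductions of 60% on vitamin C and 40% on placebo, with amputees scored as 0%. Amputation of 15% on placebo and 5% on vitamin C gives 0.95 × 60 − 0.85 × 40 = 23 points with amputees kept, against 20 without them. With 5% and 2% it is 0.98 × 60 − 0.95 × 40 = 20.8 against 20. With 5% in both groups it is 57 − 38 = 19 against 20. Size and direction both change with the rates, and 2.7.3 gives a not-healed status, not a 0% score.

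**Conclusion.** The point holds for outside vitamin C. As written, 2.15 keeps a fully capsule-compliant placebo participant who supplements outside the trial, under any reading of the denominator. If outside vitamin C had the full effect, each 10% of placebo participants affected would dilute the per-protocol contrast by up to about 10%. The loss is smaller if the outside dose is lower or starts late. How often this will happen is unknown from the documents.

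The early-stopping matter is a clarification only. If the denominator is the full course, the per-protocol result is an effect in treatment completers and should be described so. The documents do not support a claim of bias of known size or direction.

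Severity is low: the sample size, the primary intention-to-treat analysis and the complete-case check do not depend on how this set is defined.

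**What to change.** In 2.15, define the per-protocol set as participants who are more than 90% capsule compliant and have no non-trial vitamin C supplement recorded at any fortnightly visit. The data are already collected under 2.10. The cost is one sentence, a slightly smaller set and one more post-randomisation exclusion, with intention-to-treat remaining primary. Settle it before unblinding, since section 3.1 expects data collection to end by June 2026 and a rule chosen afterwards could look driven by the data.

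For clarity, state in 2.11 whether the denominator is the full 112 capsules and, if so, describe the per-protocol result as applying to treatment completers.

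A denominator pro-rated to the day of withdrawal should not be adopted as a remedy. Someone who withdraws on day 3 after 6 of 6 capsules would score 100% and enter the set with no 8-week outcome.

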### Handling of Withdrawals

2.12

When scenarios of participant withdrawal occur for reasons such as voluntary withdrawal, medical withdrawal (including undergoing amputation), protocol violation and/or adverse events, the participant's data will be included in an ‘intention to treat’ analysis (as detailed below in 2.15). No data substitution will be applied for reporting of adverse events or intervention adherence.

### Data Management

2.13

Identifiable and re‐identifiable data will be stored separately and securely at Monash Health and at Deakin University. Hard copy data will be stored in a locked filing system at each of the study sites. All de‐identified research data will be entered directly into REDCap [30] and will be stored on a secure password protected server on the Deakin University Research Data Store. Access to all data will be restricted to members of the research team. Data will be stored for a period of 15 years after final publication of research outcomes. The collected blood samples will be labelled with codes and either measured immediately or frozen in aliquots and stored at −80 degrees Celsius at Monash Health and Deakin University for batch analysis at study completion. Following analysis at Monash Health, any remaining sample will be destroyed. At Deakin University, any left‐over plasma samples will be kept for up to 15 years and may be used for other purposes in the future closely aligned with the original research (micronutrients, oxidative stress biomarkers).

### Sample Size

2.14

Sixty‐eight participants (*N* = 34 per treatment group) will allow for the detection of differences between treatments for the primary outcome measure of percentage reduction in ulcer size after 8 weeks of treatment. Since standard deviation (SD) values have not been published for the primary outcome measure, we assumed a large effect size of Cohen's *d* = 0.80 (*α* = 0.05, two‐tailed), with estimated power of 90%. The chosen effect size was based on prior studies that have either reported ulcer size healing after several weeks of vitamin C treatment or placebo [22] or the difference in ulcer size reduction for ulcers that healed compared to those that did not heal following several weeks of standard care [54]. Therefore, to account for an expected 15% participant withdrawal, we will recruit 80 participants to ensure sufficient power for our primary outcome measure. This sample size will also provide 90% power to detect a minimum 3.5 hazard ratio for time to 50% ulcer healing, assuming censoring of 70% in the control group [22].

Estimated power is ≥ 99% for the secondary outcome measure of 50% increase in plasma vitamin C levels after 8 weeks of treatment (mean difference = 48 μmol/L, SD = 19 μmol/L) [33] (*α* = 0.05, two‐tailed). To inform sample size calculations for future RCTs, exploratory outcome measures will also be collected at baseline and at the end of the treatment with estimated power to detect clinically meaningful differences for the following measures being between 27% and 61% (HbA1c, fasting glucose, systolic blood pressure, mental health and well‐being surveys).

